#### 7.3.3 Subject Compliance Monitoring

Prior to discharge on Day -7 to -1 (screening) owners will be trained on proper use and handling of nebulizer and drug. Owners will go home with a paper copy of “Owner Administration Instructions for Inhaled IL-15” which includes links to training videos. Proper training will be documented on a training log. Owners will complete and return a “Daily Drug Administration Diary” logging Inhaled IL-15 treatments. Failing to comply with treatment regimens and scheduled visits will be grounds for discontinuation in the study.

#### 7.3.4 Protocol Deviations

Any excursions from this protocol will be captured on a Protocol Deviation form and reviewed by the Principal Investigator.

### 7.4 *Clinical Procedures / Assessments*

See Visit Descriptions

### 7.5 *Laboratory Procedures / Assessments*

See Appendices at the end of the document as well as separate SOP Appendix companion document.

## 8 Statistical Plan

### 8.1 *Sample Size Determination*

Hypothesizing an improvement in ORR from 11% to 50% using conditioning chemotherapy, a sample size of 10 provides 80% power to detect this difference between our historical ORR (the null hypothesis) and the higher ORR of interest at the 0.05 level (1-sided). Therefore, using this study design, it is unlikely that treatments producing modest improvements in ORR will be selected for follow up testing

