| Number of Subjects                    | 10                                                                                                                                                                                       |
| Diagnosis and Main Inclusion Criteria | Dogs with pulmonary metastasis greater than 1cm.                                                                                                                                         |
| Study Product, Dose, Route, Regimen   | Recombinant Human Interleukin-15 (IL-15), 50ug, inhalation, twice daily for 2 weeks. Doxorubicin (30mg/m2 or 1mg/kg depending on clinician prescription), IV on Day 0.                   |
| Duration of participation             | 98 Days                                                                                                                                                                                  |
| Reference therapy                     | Doxorubicin                                                                                                                                                                              |
| Outcome measures                      | Laboratory test values, physical examination, owner questionnaire.                                                                                                                       |

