### ***1.3 Rationale and Risk/Benefits***

Dogs with lung metastases secondary to melanoma or osteosarcoma have a dismal prognosis and response rates to standard chemotherapy are less than 20% for most tumor types. Therefore, these patients are ideal candidates for novel therapies. Previous studies have demonstrated durable responses to inhaled IL-15 in dogs with metastatic osteosarcoma or melanoma without any recognized toxicity. If successful, this trial will provide important evidence in a large animal, outbred model of spontaneous metastasis that preconditioning chemotherapy with doxorubicin treatment followed by immunotherapy with inhaled IL-15 is a safe and potentially effective treatment for dogs with lung metastasis.

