## **2 Study Objectives**

### ***2.1 Primary Objective***

To determine whether preconditioning lymphodepletion with doxorubicin will improve response rates to inhaled IL-15 in dogs with lung metastases.

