##### Start Inhaled IL-15 Therapy:

- Physical examination
- Quality of life assessment form
- 13 mL of blood obtained for CBC, Chem and PBMC's
- CBC evaluated by trials clinician
  - No minimum cell requirements for IL-15 administration, but if clinically unwell from doxo, may delay
- Inhaled IL-15 (50ug) started in hospital followed by 2 hours monitoring (See XXX section for monitoring details)
- 14 days' supply of IL-15, required PPE, IL-15 Administration Diary sent home with owner

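### The test in section 8.1 can show that doxorubicin plus IL-15 beats a historical response rate, but not the stated objective that lymphodepletion improves response to IL-15

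*Protocol*

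**What the plan says.** Section 2.1 gives the primary objective: "To determine whether preconditioning lymphodepletion with doxorubicin will improve response rates to inhaled IL-15 in dogs with lung metastases". The Study Summary and section 3.1 repeat it. Section 3.1 also makes the trial single-arm and non-randomized, and section 6.2 gives every dog doxorubicin on Day 0 and IL-15 from Day 7.

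Section 8.1 contains the only comparison: "Hypothesizing an improvement in ORR from 11% to 50% using conditioning chemotherapy". The two rates are described as "our historical ORR (the null hypothesis) and the higher ORR of interest", and "a sample size of 10 provides 80% power to detect this difference" at a one-sided 0.05 level. The source of the 11% is not stated. The reference to adding conditioning chemotherapy implies a rate for IL-15 without conditioning, and it is read that way here.

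Section 1.3 says that "response rates to standard chemotherapy are less than 20% for most tumor types". The Study Summary enters doxorubicin under "Reference therapy", but no doxorubicin response rate appears in section 8.1. The primary endpoint (section 3.2) is objective radiographic response. Baseline films are taken at or before Day 0, none is scheduled on Day 7, and the next are on Days 35 and 49 (sections 7.1 and 7.2).

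**The concern.** The objective is a claim about cause: that depleting lymphocytes makes IL-15 work better. The test asks only whether dogs given both drugs respond more often than a historical rate. The agent used for conditioning may shrink tumours directly. Because the baseline film precedes doxorubicin and no film is taken when IL-15 starts, a direct response to doxorubicin is counted exactly like a response to conditioned IL-15.

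A result that rejects 11% would therefore answer a narrower question than section 2.1 asks. If it were read as an answer to section 2.1, follow-up work could be built on a conditioning effect when two separately active drugs would explain the result.

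**Working it through.** **Inputs.** From section 8.1: n = 10, null 0.11, alternative 0.50, one-sided 0.05. From section 1.3: standard chemotherapy below 20% for most tumor types. Assumed: a doxorubicin-alone response rate d between 0% and 20%, because the protocol gives no figure for doxorubicin in these dogs. Derived: the cut-off, because section 8.1 states none.

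**Step 1: reproduce the plan.** With X binomial (10, p):

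- At p = 0.11, P(X ≤ 3) = 0.3118 + 0.3854 + 0.2143 + 0.0706 = 0.9822, so P(X ≥ 4) = 0.0178. A cut-off of 3 gives 0.088, above 0.05, so the rule is at least 4/10.
- At p = 0.50, P(X ≥ 4) = 1 − (1 + 10 + 45 + 120)/1024 = 0.828.

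The stated 80% power is met, with exact type I error 1.8%.

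**Step 2: suppose conditioning adds nothing.** If the drugs act independently, the combined rate is p = 1 − (1 − 0.11)(1 − d).

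| d (assumed) | combined p | P(X ≥ 4 of 10) |
|---|---|---|
| 0% | 0.110 | 1.8% |
| 5% | 0.1545 | 5.5% |
| 10% | 0.199 | 11.9% |
| 15% | 0.2435 | 20.9% |
| 20% | 0.288 | 31.9% |

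For the last row, P(X ≤ 3) = 0.0335 + 0.1354 + 0.2465 + 0.2659 = 0.6813, which leaves 0.319.

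**Step 3: where 5% is crossed.** P(X ≥ 4) = 0.050 at p = 0.150. Solving 0.15 = 1 − 0.89(1 − d) gives d = 1 − 0.85/0.89 = 4.5%.

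**Step 4: how far independence matters.** At d = 20%:

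- If no dog would respond to both drugs, p = 0.11 + 0.20 = 0.31 and the chance is 37.7%.
- If every dog that responds to IL-15 would also respond to doxorubicin, p = 0.20 and the chance is 12.1%.

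The 5% crossing moves in the same way: d = 0.15 − 0.11 = 4% with no overlap, and d = 15% with full overlap.

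**Step 5: what a null allowing for doxorubicin would require.** With 10 dogs, a null of 20% (d of about 10%) needs at least 5/10, with power 62%. A null of 28.8% needs at least 6/10, with power 38%. The smallest n giving 80% power at 50% is 17 (at least 7 responses) against 20%, and 34 (at least 15) against 28.8%.

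**The case against.** **The top of the range is a limiting case.** This stands. Section 1.3 says less than 20%, speaks of standard chemotherapy in general, and does so to explain a dismal prognosis. Dogs here receive one dose, and prior doxorubicin is allowed, which may lower its activity. The cut-off and the independence assumption are also not in the protocol. The figure has to be given as a range that starts at 1.8%.

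**The 32% is not a type I error.** A reader might infer that the stated 0.05 level or the sample size is wrong. The documents do not support that. For the hypothesis in section 8.1 the error is 1.8%, and if the combination's true rate were 28.8%, rejecting 11% would be correct. The 32% is the chance of a result that could be wrongly credited to lymphodepletion.

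**A high count would still be informative.** A reader might infer that no result could bear on conditioning. That goes too far: 6 or more responses in 10 has probability 3.9% even at 28.8%. But the planned test does not require 6.

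**The protocol already holds a modest claim.** Section 1.1 speaks of preliminary evidence of efficacy for the combination, and section 8.1 of selection for follow-up testing. Nothing says that 4/10 would be reported as proof of preconditioning. This stands, and it gives the wording for the fix. It does not remove the mismatch, because the Study Summary and sections 2.1 and 3.1 still set the causal question.

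**No analysis of lymphocyte counts is described.** A reader might count this as a defect and cite the Day 7 line "No minimum cell requirements for IL-15 administration". That line concerns whether IL-15 may be given, not analysis, and an exploratory summary may properly be left to an analysis plan that is not shown.

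**Conclusion.** The stated objective and the planned test do not match, and the mismatch is fixed in the protocol itself by the objective, the single arm and the null value. Rejecting 11% would support the statement that the combination's response rate exceeds the historical rate. It would not show that lymphodepletion caused the gain.

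The calculation in section 8.1 is sound for its own hypothesis. What fails is carrying its 0.05 level over to section 2.1. With no conditioning effect, the chance of at least 4/10 is 1.8% to at most about 32%, and it exceeds 5% once doxorubicin alone achieves more than about 4.5%. These figures rest on the derived cut-off, on independent action, on an assumed doxorubicin range of 0% to 20%, and on reading the 11% as IL-15 without conditioning.

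**What to change.** - Reword the Study Summary objective and sections 2.1, 3.1 and 8.1, in line with section 1.1, so that the primary conclusion is whether the combination's response rate exceeds the historical 11%. State that success will not by itself be attributed to lymphodepletion.
- State in section 8.1 where the 11% comes from and which treatment it describes.
- Give the misattribution range (1.8% to at most about 32%) with its assumptions.
- Reconcile the Study Summary's doxorubicin reference-therapy entry with the historical comparator that section 8.1 actually uses.
- Optionally, report the Day 0 to Day 7 change in lymphocyte count descriptively, from the CBCs already scheduled. This checks that depletion occurred. It does not separate a direct cytotoxic response from conditioning.

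The cost is wording, plus one descriptive summary if wanted. The number of dogs, the test, the endpoint and the visits are unchanged. The downside is a weaker headline claim. Raising the null to allow for doxorubicin's own activity would instead take 17 to 34 dogs for nulls of 20% to 28.8%, and would still rest on an assumed doxorubicin rate.

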### 8.2 *Statistical Methods*

[Summarize the statistical analysis approach for the trial. Detail the analysis of both primary and secondary endpoints.]

CONFIDENTIAL

This material is the property of the University of California. Do not disclose or use except as authorized in writing by the study sponsor.

### 8.3 *Subject Population(s) for Analysis*

per-protocol/protocol compliant (starting inhaled IL-15)

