### 5.7 *Early Withdrawal of Subjects*

#### 5.7.1 When and How to Withdraw Subjects

Subjects may be withdrawn at the request of the caregiver, due to adverse events, and/or at the investigator's discretion. If any patient becomes increasingly sick, and the quality of life is of concern to the study staff, discussions will occur to determine how to proceed.

The investigator may remove the subject from the trial if their caregivers fail to bring them to scheduled study visits and/or provide data and the caregivers cannot be reached by the study site for 2 weeks. Alternatively, if caregiver cannot consistently give the patient the twice daily inhaled dose of IL-15, they may be removed from the study.

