- Physical examination and confirmation of eligibility
- Quality of life assessment form
- 11.5 mL blood will be collected for PBMCs and CBC
- Obtain baseline thoracic radiographs (sedation likely required)
- Bloodwork evaluated for adequacy by primary clinician prior to chemotherapy administration
- Doxorubicin @ 30mg/m^2 or 1mg/m^2 IV depending on clinician prescription, both prepared and administered by medical oncology staff
- Patient sent home under owner's care
- Client provided chemosafety information and routine PRN meds

#### 7.2.3 Follow-up – Visit Day 7

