#### 7.3.1.2 Concomitant Therapy

Non-study medications/treatments are prohibited during the trial period. Exceptions are as described above (NSAIDS for pain control acceptable if patient has received for > 2 weeks, pamidronate or zoledronate also permitted). Any non-study medications will be captured on the Concomitant Therapy Form.

CONFIDENTIAL

This material is the property of the University of California Do not disclose or use except as authorized in writing by the study sponsor

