#### 7.3.1.3 Rescue Therapy

No rescue therapy is available for metastatic osteosarcoma and melanoma, however the patient can be withdrawn from the trial to pursue other therapeutic options.

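### The only analysis set starts at the first IL-15 dose, so dogs that fail after doxorubicin but before IL-15 leave the ORR denominator and bias the response rate upward

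*Protocol*

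**What the plan says.** Section 8.3 defines the population for analysis in one line: "per-protocol/protocol compliant (starting inhaled IL-15". No all-enrolled or all-treated set is named, and nothing is said about how dogs that never start IL-15 are counted or whether they are replaced. Section 8.2 (Statistical Methods) still holds template text, so it does not bring those dogs back.

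Section 6.2 gives doxorubicin to all enrolled dogs on Day 0 and starts inhaled IL-15 on Day 7. At the Day 7 visit (section 7.2.3) the start depends partly on how the dog has tolerated doxorubicin: "No minimum cell requirements for IL-15 administration, but if clinically unwell from doxo, may delay". Section 5.7.1 allows withdrawal for adverse events, at the caregiver's request or at the investigator's discretion. The primary endpoint (section 3.2) is radiographic ORR. The first radiographs after baseline are scheduled for Day 35.

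Section 8.1 sets the test: "Hypothesizing an improvement in ORR from 11% to 50% using conditioning chemotherapy", one-sided at 0.05, and states that "a sample size of 10 provides 80% power to detect this difference".

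**The concern.** The question is whether doxorubicin preconditioning followed by IL-15 gives a better response rate than the historical one. Doxorubicin is part of that regimen, yet entry to the analysis set is decided at least a week after it is given, by an event that doxorubicin itself can influence. A dog lost in that interval has no response assessment, so dropping it cannot reduce the numerator; it only reduces the denominator. The comparison is with a fixed 11% and there is no concurrent arm in which the same selection could cancel out.

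With ten dogs, one or two exclusions matter. At stake is whether the trial is declared a success. Section 8.1 argues that the design makes it unlikely that a treatment with only a modest gain goes forward, and this analysis set weakens that protection.

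**Working it through.** **Inputs.** From section 8.1: null ORR p0 = 0.11, target p1 = 0.50, N = 10, one-sided alpha 0.05. From section 8.3: the denominator is the dogs that start IL-15. The non-start rate is not given; every value used below is an assumption.

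**Formula.** Exact binomial tail, P(X ≥ r | n, p) = 1 − Σ C(n,k) p^k (1−p)^(n−k), summed over k = 0 to r−1. The critical value is the smallest r with P(X ≥ r | n, 0.11) ≤ 0.05.

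**The plan's own figure.** For n = 10, P(X ≥ 3 | 0.11) = 0.0884 and P(X ≥ 4 | 0.11) = 0.0178, so the rule is at least 4 of 10. Power is P(X ≥ 4 | 10, 0.50) = 0.828. The stated 80% is met.

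**Effect on the verdict with 3 responders.**
- 3/10: 1 − (0.3118 + 0.3854 + 0.2143) = 0.088, not significant.
- 3/9 (one non-starter): 1 − (0.3504 + 0.3897 + 0.1927) = 0.067, not significant.
- 3/8 (two non-starters): 1 − (0.3937 + 0.3892 + 0.1684) = 0.0487, significant.

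**False-positive probability.** Suppose the true ORR in all treated dogs is 11% and non-starters do not respond. With exactly two of ten excluded, the rate among starters is 0.11 × 10/8 = 0.1375 and the rule becomes at least 3 of 8. P(X ≥ 3 | 8, 0.1375) = 1 − (0.3062 + 0.3906 + 0.2179) = 0.085. With one excluded, the rule is at least 4 of 9 and the probability is 1.7%. With all ten dogs kept it is 1.8%. Averaged over a random number of non-starters, at assumed non-start rates of 5%, 10%, 20% and 30%, it is 2.2%, 3.1%, 5.2% and 7.1%.

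**If non-starters are replaced until ten dogs start.** A result of 4/10 gives p = 0.0178. Counted over all treated dogs, 4/13 gives p = 0.0464 and 4/14 gives p = 0.0594, so four replaced dogs are needed before the two denominators disagree.

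**Power with all doxorubicin-treated dogs as the denominator.** The rule stays at 4 of 10. If starters respond at 50% and non-starters count as failures:
- 10% non-start (assumed): overall ORR 0.9 × 0.5 = 0.45, P(X ≥ 4 | 10, 0.45) = 73%.
- 20% non-start (assumed): overall ORR 0.8 × 0.5 = 0.40, P(X ≥ 4 | 10, 0.40) = 62%.

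**The case against.** The set has a rationale. The primary objective concerns response to inhaled IL-15, and a historical rate obtained with IL-15 is most naturally compared with dogs that received it. That is a good reason to report IL-15 starters, but not to make them the only set. The protocol does not say how the 11% was counted, and nothing indicates that those dogs first had to get through a week after doxorubicin.

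The change of verdict is narrow. It needs 3 responders and at least two non-starters; with 4 or more responders out of ten the trial succeeds on either denominator. Screening covers organ function, MDR status and cardiac disease, so early losses may be few. A delayed dog that later starts stays in the set. All of this stands, and it limits the size of the bias but not its direction.

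Several stronger readings are tempting but not supported:
- **That 80% power needs all ten dogs to start.** Under the protocol's own set, power at 50% ORR is 74.6% with 9 starters but 85.5% with 8, because the critical value falls to 3. The 73% and 62% above belong to the all-treated denominator.
- **That every excluded dog is a treatment failure.** Section 5.7.1 says "if caregiver cannot consistently give the patient the twice daily inhaled dose of IL-15, they may be removed from the study", and an owner may withdraw for practical reasons. Neither is necessarily a failure of treatment.
- **That dogs leaving after IL-15 has begun are also dropped.** The parenthesis in section 8.3 can be read as defining compliance by having started. On that reading, a dog removed for missed nebulisations stays in, as does one withdrawn later under section 7.3.1.3, where "the patient can be withdrawn from the trial to pursue other therapeutic options".
- **That using PRN medicines makes a dog non-compliant.** Section 7.3.1.2 states "Non-study medications/treatments are prohibited during the trial period", while the Day 0 visit lists "Client provided chemosafety information and routine PRN meds". The PRN supply is part of the protocol's own visit, and no passage says that its use removes a dog from analysis.
- **That early doxorubicin toxicity is lost.** Section 9 records all adverse events from screening onward. Section 8.3 does not say whether its set governs toxicity, so this is unclear rather than wrong.

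**Conclusion.** The point holds for dogs that fail between doxorubicin and the first IL-15 dose. Section 8.3 states a rule that removes them from the ORR denominator and can only push the rate upward. This is a choice the protocol makes, not a detail deferred to a later document.

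The size depends on assumptions. Two such losses without replacement are enough to turn a failed 3/10 into a significant 3/8 and give an 8.5% false-positive probability. That figure is conditional on exactly two non-responding non-starters; averaged over assumed non-start rates, the probability passes 5% only at about 20% or more. With replacement, about four losses are needed to change a 4/10 result. In a ten-dog trial with no stated non-start rate or replacement rule, the primary denominator should be settled before data are seen.

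**What to change.** - **Section 8.3, efficacy.** Make all dogs given doxorubicin on Day 0 the primary ORR set, and count any dog without an evaluable post-baseline radiograph as a non-responder. This convention is conservative for dogs that leave for non-clinical reasons. Keep the IL-15-started set as supportive, for comparison with the historical rate.
- **Section 8.3, toxicity.** State that toxicity is reported in all doxorubicin-treated dogs.
- **Section 8.1.** State that the power (82.8% exact, rule at least 4 of 10) assumes a 50% ORR among all ten dosed dogs, and show 73% and 62% for assumed non-start rates of 10% and 20% with starters responding at 50%.

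The cost is protocol wording, with no extra dogs, visits or measurements. The downside is a slightly lower reported ORR and a less favourable power statement.

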## 9 Safety and Adverse Events

### 9.1 *Definitions*

#### **Adverse Event (AE)**

An *adverse event* (AE) is any symptom, sign, illness or experience that develops or worsens in severity during the course of the study. Intercurrent illnesses or injuries should be regarded as adverse events. Abnormal results of diagnostic procedures are considered to be adverse events if the abnormality:

- results in study withdrawal
- is associated with a serious adverse event
- is associated with clinical signs or symptoms
- leads to additional treatment or to further diagnostic tests
- is considered by the investigator to be of clinical significance

#### **Serious Adverse Event (SAE)**

Adverse events are classified as serious or non-serious. A *serious adverse event* (SAE) is any AE that is:

- fatal
- life-threatening
- requires or prolongs hospital stay
- results in persistent or significant disability or incapacity
- an important medical event

Important medical events are those that may not be immediately life threatening, but are clearly of major clinical significance. They may jeopardize the pet and may require intervention to prevent one of the other serious outcomes noted above. All adverse events that do not meet any of the criteria for serious should be regarded as *non-serious adverse events*.

